### Data collection and management

#### Data collection

Data are collected at the individual level (demographic data, data collected using standardized tools/questionnaires), household level (information on the head of the family, structured questionnaires, daily records of use of the CSF) and village (community) level. Field-based data collection will be paper-based and will be done by trained data collectors. Prior to starting data collection, all research staff will be trained in protection of human subjects, good clinical practice guidelines and administration, data entry and analysis of study-specific data collection tools. All the data collectors, trainers and research officers will receive refresher training at regular intervals to ensure data quality and adherence to intervention protocol. The YAM follow-up data collection schedule will be explained to the parents of child participants at the time of the informed consent/assent procedure. Quarterly review and facilitation meetings will be organised at the village level for retaining the participants in the CSF and mhGAP intervention. Three follow-up visits will be conducted if participants are absent for whatever reason when the data collection is due. Written Informed consent will be sought from all participants. Consent of an illiterate participant will be obtained in the presence of a literate impartial witness according to the guidelines of the Indian Council of Medical Research [39]. In intervention 1, consent of one of the parents and assent of the adolescent will be obtained. For intervention 2, consent of the head of the household (one who manages the use of pesticides at home) will be sought. Similarly, consent of the head of the household will be sought for collecting data on use of community storage boxes. For intervention 3, consent of all the CHWs will be obtained only for data collection. For surveillance data collection consent of all the key informants will be obtained. Each study participant will receive a 5-digit alphanumeric unique study ID. The collected data will be de-identified prior to entry into the electronic database.

#### Data management

SPIRIT will develop and implement a comprehensive data management system allowing for collecting high-quality data by maintaining ongoing on-site and off-site quality assurance and quality control checks. Research staff handling study data will receive extensive training in procedures for handling sensitive information, accurate data entry, surveillance and intervention-specific data storage and data archive. All completed forms will be checked for completeness and accuracy, first by data collectors and later by a research associate responsible for data management. During monthly monitoring visits, the data manager will audit hard copies of the completed CRFs to check for completeness and accuracy. Prior to entering the data into an electronic data capture interface, all study data will be anonymized. A separate record will be maintained linking identifiable information and unique study IDs. Participant-specific data will be entered into the electronic data capture interface using only study IDs. Data entered will be cross-checked and an audit trail will be maintained if corrections in the data are warranted. Raw data will not be uploaded onto the Internet; instead an electronic data capture interface will function offline, and data will be transferred from Mehsana to Pune (where the project coordination office is) from the site on a monthly basis using encrypted and protected hard drives. The data manager will maintain the database with cleaned data, which will be used by the statistician based in Pune for data analysis.

#### Data storage, security and confidentiality

All consent and assent forms and records of personally identifiable information will be kept confidential and protected from unauthorized access. Hard copies of the CRFs obtained from the surveillance system will be stored by month of surveillance, whereas hard copies of the interventions-specific data will be stored by village where the data were collected. All data will be kept in locked cupboards, accessible by key only by the data management staff and the principal investigators only.

#### Data monitoring

The trial is monitored by an independent DSMB. The DSMB is made up of five members and consists of independent experts in biostatistics, health services research, medical ethics, public health, social science research and clinical trials within the Indian context; it will meet twice a year to oversee the trial. The trial is also subject to quarterly independent quality assurance audit of the performance of the site as per the guidelines of the funding agency.

### Data analysis and reporting

All findings from the trial will be reported in accordance with SPIRIT, Extended CONSORT and CHEERS guidelines. For analysis of quantitative data, we will first tabulate descriptive statistics for all study variables to understand trends in the data. For efficacy analysis of the primary outcome, we will apply an intention-to-treat (ITT) approach to all participants assigned to the intervention arm as randomised, regardless of the study intervention received. We will test the null hypothesis of no difference in the population incidence of suicides and attempted suicides between clusters allocated to the intervention and control arms, using surveillance data.

A multilevel Poisson regression model will be employed, with inflated standard error to accommodate the clustered design. Inflation will be achieved using a normal or gamma distributed random effect, whichever best describes the variation in number of suicides across villages. Change in suicide and attempted suicide rates from baseline to follow-up (12 months) at intervention and control sites will be calculated separately, adjusting for random cluster effect. We will compare this change in the intervention and control arms and calculate the 95% confidence interval.

If there is statistical evidence of over-dispersion in the Poisson regression model, a negative binomial regression analysis will be performed. Allowance will be made if a greater than expected number of clusters without a case of suicide/suicide attempt is observed, using the Stata zero-inflated negative binomial regression (“zinb”) command or zero truncated Poisson regression for instance, which includes a test of whether this approach offers an improvement over the standard model. All hypothesis testing will be carried out at the 5% (two-sided) significance level. *P* values will be rounded to 2 decimal places. *P* values below 0.05 will be reported as < 0.05 in tables.

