#### Intervention 1: YAM in schools: primary outcome

Suicidal ideation among young adolescents in both intervention and control condition schools will be assessed using the Suicidal Ideation Attributes Scale (SIDAS) [32]. SIDAS is a 5-item self-report scale addressing attributes of suicidal thoughts: frequency, controllability, closeness to attempt, level of distress associated with thoughts and impact on daily functioning. Scores ≥ 21 indicate a high risk of suicidal behaviour among youths. In this study, the SIDAS score will be assessed at baseline and at 3-month and 12-month follow-up. If a student has elevated scores on suicidal ideation (≥ 21 out of a maximum score of 50) at baseline assessment, he/she will be referred to the closest locally available health services such as a primary care centre, district mental health hospital or the Hospital for Mental Health in Ahmadabad (tertiary specialised mental health hospital).

Depression symptoms will be assessed using the Patient Health Questionnaire-9 (PHQ-9), a 9-item self-report scale [33, 34]. The PHQ-9 will be administered to students in the intervention and control schools at baseline and 3-month and 12-month follow-up. PHQ-9 scores range from 0 to 27 with higher scores indicating greater symptom severity. Scores of 5, 10, 15 and 20 represent cut-offs for mild, moderate, moderately severe and severe depression, respectively. Students who meet criteria for severe depression (scores > 20 on the PHQ-9 scale) at baseline assessment will be referred to the closest locally available health services such as a primary health centre, district mental health hospital or the Hospital for Mental Health in Ahmedabad (tertiary specialised mental health hospital).

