#### Specific analysis for each intervention

For intervention 1, differences in PHQ-9 and SIDAS scores at 12-month follow-up between students in the intervention and control arms will be calculated using a multilevel, linear effect model adjusting for clustering by villages as a random effect. We will analyse the SIDAS scores both on a continuous and categorical scale. Parameters for categorical variables will be either no ideation versus ideation or tertile scores (low/medium/high).

For intervention 2, all the secondary outcome data as per Table 1 will be analysed and presented as summary tables using count data and logs maintained by research team. Additionally, data from survey responses from a structured questionnaire from four villages (two control, two intervention) will be analysed pre and post intervention to evaluate pesticide purchase, storage options and acceptability and use of the CSF in the intervention villages.

For intervention 3, due to the ordinal nature of the data (knowledge, skills and attitude scales), multilevel ordered logistic regression (ordinal logistic regression) will be employed to assess change in knowledge, skills and attitude from baseline to follow-up in both intervention and control groups. Adjusted and unadjusted estimates will be reported as the proportional odds ratio or log odds coefficient. The number of persons with suicidal ideation detected and referred on by trained CHWs will be recorded as count data through logs and daily record registers. All the count data will be analysed using descriptive statistics.

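### The primary effect is reported as a difference in change from baseline, and the school model states no baseline term; adjusting for baseline would be clearer and more precise

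*Protocol article*

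**What the plan says.** All references are to the protocol article.

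**Primary outcome, Data analysis and reporting.** The hypothesis is about incidence: "We will test the null hypothesis of no difference in the population incidence of suicides and attempted suicides between clusters". The model is named next: "A multilevel Poisson regression model will be employed, with inflated standard error to accommodate the clustered design". The reported effect is then put in terms of change: "Change in suicide and attempted suicide rates from baseline to follow-up (12 months) at intervention and control sites will be calculated separately", with an allowance for the random cluster effect, followed by "We will compare this change in the intervention and control arms and calculate the 95% confidence interval". No baseline covariate is named. The testing level is given once for everything: "All hypothesis testing will be carried out at the 5% (two-sided) significance level".

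**Sample size for intervention 2.** The calculation compares rates after the intervention (10 per 1000, reduced by 20%). It has no baseline term.

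**School outcome.** The section on the YAM primary outcome says that "the SIDAS score will be assessed at baseline and at 3-month and 12-month follow-up", and likewise "The PHQ-9 will be administered to students in the intervention and control schools at baseline and 3-month and 12-month follow-up". The use it gives for the baseline scores is referral of students with high scores. Under Specific analysis for each intervention, "differences in PHQ-9 and SIDAS scores at 12-month follow-up between students in the intervention and control arms will be calculated" with a multilevel linear model that has village as a random effect. No other adjustment is stated there for this analysis. Adjusted and unadjusted estimates are mentioned only for intervention 3.

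**The concern.** Two things are at stake.

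**Clarity.** The hypothesis and the sample size are about follow-up incidence, while the interval is about a difference in changes. The text does not say that both come from one model, or which quantity decides the primary result.

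**Precision.** A village's baseline count is a noisy measure of its underlying rate. A change contrast gives that count full weight and so brings all of its noise into the comparison. Entering the baseline rate as a covariate gives it only the weight its correlation with follow-up supports. For the schools, a baseline score already in hand would explain part of the spread in 12-month scores, and the stated model does not use it.

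**Working it through.** **1. The plan's own figures.**
- Design effect for the primary outcome: 121,820 / 60,901 = 2.00. The attrition step follows: 121,820 × 1.2 = 146,184.
- The 60,901 itself does not reproduce from 1.0% against 0.8% (the usual two-sided calculation gives 70,002 in total). That is a separate matter; only the ratio 2.00 is used here.
- School sample: 19% against 15%, two-sided 5%, 80% power, with continuity correction gives 1,433 per arm, 2,866 in total; × 1.59 = 4,557. Both match the plan.

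**2. Relative variances.** Take equal variance at baseline and follow-up, with correlation ρ between a village's observed baseline and follow-up rates. Set the follow-up-only contrast to 1.
- Change: 1 + 1 − 2ρ = 2(1 − ρ)
- Baseline as covariate: 1 − ρ²
- Change / covariate: 2(1 − ρ) / [(1 − ρ)(1 + ρ)] = 2/(1 + ρ)

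The last ratio exceeds 1 for every ρ below 1. Change is also less precise than follow-up only when 2(1 − ρ) > 1, that is, when ρ < 0.5.

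**3. How large ρ can be.** 121,820 / 124 = 982 persons per village. With equal village sizes (the plan gives no coefficient of variation), a design effect of 2.00 implies an intra-cluster correlation of 1.00 / 981 = 0.00102. About half of the variance of an observed village rate is then between villages: (982 × 0.00102) / 2.00 = 0.50. So ρ is 0.50 times the persistence of true village rates from baseline to follow-up, and is at most about 0.50.

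**4. Size at 982 persons per village.** Power = Φ(2.80/√variance − 1.96), starting from 80% for follow-up only.

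| Persistence | ρ | Change | Covariate | Ratio | Power, change | Power, covariate |
|---|---|---|---|---|---|---|
| full | 0.50 | 1.00 | 0.75 | 1.33 | 80% | 90% |
| half | 0.25 | 1.50 | 0.94 | 1.60 | 63% | 82% |
| none | 0 | 2.00 | 1.00 | 2.00 | 51% | 80% |

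**5. Size at 2,509 persons per village,** the census figure in the sample size section. With the same intra-cluster correlation, the design effect is 1 + 2,508 × 0.00102 = 3.56 and the between-village share is 2.56 / 3.56 = 0.72. With full persistence the ratio is 2 / 1.72 = 1.16.

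**6. Simulation check.** 62 + 62 villages, 10 per 1000, rate ratio 0.8, between-village coefficient of variation 0.32 (from the design effect), an assumed 12-month baseline, analysis of village log rates, 1,500 runs per setting. Power for follow-up only / change / covariate:

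| Persistence | 982 per village | 2,509 per village |
|---|---|---|
| full | 72 / 71 / 82% | 91 / 97 / 99% |
| 70% | 72 / 61 / 77% | 91 / 88 / 96% |
| 40% | 73 / 51 / 74% | 91 / 77 / 92% |

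The covariate analysis had the highest power in every setting. Change beat follow-up only in one: large villages with fully stable rates.

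**7. School scores.** For a continuous score with baseline to 12-month correlation r, adjustment multiplies residual variance by about 1 − r². An assumed r of 0.4 to 0.6 gives 0.84 to 0.64, a reduction of 16% to 36%.

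**The case against.** **The change contrast is valid and does use baseline.** This stands. Under randomisation it is unbiased, and the loss is only relative to a better use of the same data. There is also a design reason for it: Village Councils agree after allocation and some refusals are expected, so the arms could differ at baseline, and a change contrast removes stable village differences. That is a reason to keep reporting it. It is not a reason to make the less precise contrast the only stated effect.

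**Test and interval may come from one model.** This also stands. A joint model of baseline and follow-up counts with an arm-by-period term would supply both. A reader might infer that the test and the interval must target different quantities and can contradict each other. The text does not establish that; it only leaves the contrast open.

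**The school point rests on what is stated.** Covariates could be listed in an analysis plan that is not shown. A reader might infer that baseline scores are excluded from the school analysis, but the article does not say so. What can be said is that the adjustment it names does not include them.

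**The size is unknown.** This stands. In step 4, 51% power requires that village rates do not persist at all, and at that point the covariate gains nothing over follow-up only. With full persistence the change contrast keeps the 80% of a follow-up comparison. The school gain is for a continuous score and does not carry over directly to the sample size, which is for a proportion.

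**Conclusion.** The point holds as one of efficiency and clarity. The reported primary effect is a comparison of changes, while the hypothesis and the sample size concern incidence after the intervention. The change contrast has 2/(1+ρ) times the variance of a baseline-adjusted one, and it is less precise than ignoring baseline when ρ is below 0.5. With the implied design effect of 2.00 at about 982 persons per village, the ratio lies between 1.33 (fully stable village rates) and 2.0 (no persistence). At 2,509 persons per village it can be as low as about 1.16.

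The direction is certain for any ρ below 1. The size is not, because the documents give neither ρ nor the length of baseline surveillance. The figures assume baseline and follow-up periods of equal length and equal village sizes; a shorter baseline would make the change contrast noisier. The school gain of 16% to 36% of residual variance depends on the assumed correlation. The documents do not support a reading of bias, or of power having definitely fallen to about half.

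**What to change.** **Primary analysis.**
- Name the 12-month incidence rate ratio as the primary estimand.
- Take its confidence interval and p-value from one count model with arm, the village baseline rate as a covariate, a person-time offset and the planned allowance for between-village variation.
- State a rule for villages with no baseline events, since the plan expects villages without cases and the log of zero is undefined. Adding a small constant before taking logs, or using a smoothed rate, would do.
- Report the between-arm comparison of changes descriptively.

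**School analysis.** Add baseline SIDAS to the 12-month SIDAS model and baseline PHQ-9 to the PHQ-9 model, keeping the village random effect.

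**Cost.** Wording of the analysis section, plus the zero-count rule. No further data collection is needed: the school baseline scores are already planned, and the baseline rates are already required for the planned change calculation.

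### Zero-truncated Poisson regression is offered as an allowance for too many event-free villages, but it drops those villages from the primary analysis

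*Protocol article*

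**What the plan says.** All of this stands in the protocol article, under Data analysis and reporting.

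- Analysis set: "we will apply an intention-to-treat (ITT) approach to all participants assigned to the intervention arm as randomised".
- Hypothesis: the null is "no difference in the population incidence of suicides and attempted suicides between clusters allocated to the intervention and control arms".
- Main model: "A multilevel Poisson regression model will be employed, with inflated standard error to accommodate the clustered design", with a normal or gamma village effect, and negative binomial regression if there is over-dispersion.
- Trigger for the fallback: "Allowance will be made if a greater than expected number of clusters without a case of suicide/suicide attempt is observed".
- Fallback: the allowance is made "using the Stata zero-inflated negative binomial regression (“zinb”) command" or, as the second example, "zero truncated Poisson regression for instance". The sentence adds that this comes with a test of whether the approach improves on the standard model.

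The section does not describe the truncated model as one part of a two-part (hurdle) model.

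**The concern.** The remedy runs opposite to its trigger. The trigger is a surplus of villages with a count of zero; the truncated model has no place for a zero. Taken as written, the option excludes randomised villages because of their outcome. The comparison then covers only villages with at least one event, which is neither an as-randomised comparison nor a comparison of population incidence.

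The promised improvement test does not work for this option either. A truncated model is fitted to a subset of the villages, so its likelihood cannot be compared in the ordinary way with that of a model fitted to all of them.

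At stake is the primary rate ratio. If the programme changes how many villages have no events, that part of its effect is invisible to the truncated model.

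**Working it through.** The article gives no figure for this point, so there is none to reproduce.

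**1. The likelihood.** For a village with mean λ, the zero-truncated Poisson likelihood is f(y)/(1 − exp(−λ)) for y ≥ 1. A village with y = 0 contributes nothing.

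**2. What is estimated under excess zeros.** Suppose a share p of villages is always event-free and the rest are Poisson with mean μ. Given y ≥ 1, the count is truncated Poisson with mean parameter μ, whatever p is. So:

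- truncated model: μ_I / μ_C
- population incidence ratio: (1 − p_I)μ_I / [(1 − p_C)μ_C]

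The two agree if p_I = p_C. Otherwise they differ by the factor (1 − p_I)/(1 − p_C).

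- Case A: p_C = 0.20, p_I = 0.36, equal μ. Truth 0.64/0.80 = 0.80; truncated model 1.00.
- Case B: p_C = 0.36, p_I = 0.20, μ_I/μ_C = 0.80. Truth (0.80 × 0.80)/0.64 = 1.00; truncated model 0.80.

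**3. Simulation.** There were 62 villages per arm (from the sample size section for intervention 2), 4000 runs per scenario and two-sided 5% tests. The comparator is an all-village rate ratio with village-level variance. Control means per village are 3.26, 12.14 and 25.09 (from step 4, at 2509 persons). The zero shares are assumptions. Ranges run over the three means.

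| Scenario (zero share C / I) | True ratio | Truncated: ratio, rejects | All villages: ratio, rejects | Villages dropped of 124 |
|---|---|---|---|---|
| A: 20% / 36%, equal means | 0.80 | 1.00, 4.7–4.9% | 0.80, 26.5–43.0% | 34.7–38.3 |
| B: 36% / 20%, mean ratio 0.80 | 1.00 | 0.80, 37.2–99.9% | 1.00, 4.4–5.3% | 34.6–39.9 |
| C: 20% / 20%, mean ratio 0.80 | 0.80 | 0.80, 40.6–100% | 0.80, 33.4–60.5% | 24.7–30.3 |
| D: no excess zeros, mean ratio 0.80 | 0.80 | 0.80, 48.5–100% | 0.80, 55.7–100% | 0–7.0 |

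In D at mean 3.26, dropping about 7 villages lowers power from 55.7% to 48.5%. In C the truncated test rejects more often than the all-village test because it ignores variation in the zero share. That is safe only if the shares really are equal.

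A separate run of 1500 trials with shares of 10% and 28% (truth 0.72/0.90 = 0.80, mean 3.26) gave 0.998 with 5.7% rejection and 8.4 + 19.0 = 27.4 villages dropped. With ordinary gamma variation between villages (coefficient of variation 0.5, mean 1.53, true ratio 0.80) the truncated ratio was 0.814, with 16.9 + 21.4 = 38.3 villages dropped.

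**4. How likely the trigger is.** Inputs are from the sample size section for intervention 2: planning rate 10 per 1000; state suicide rate 11.8 per 100,000; attempts 10 to 40 times suicides. Village size is taken as 2509 persons (printed as household members, read here as persons per village) or 146,184/124 = 1179. The derived rates are 11.8 × 11 = 129.8 per 100,000 (1.3 per 1000) and 11.8 × 41 = 483.8 per 100,000 (4.8 per 1000). Expected event-free villages under plain Poisson are 124 × exp(−rate × size):

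| Rate | 2509 persons | 1179 persons |
|---|---|---|
| 10 per 1000 | <0.001 | <0.001 |
| 4.8 per 1000 | <0.001 | 0.4 |
| 1.3 per 1000 | 4.8 | 26.8 |

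At 10 per 1000 with a between-village coefficient of variation of 0.5 (gamma shape 4), the count is 124 × (1 + mean/4)^−4. This gives about 0.04 at mean 25.09 and 0.5 at mean 11.79.

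**The case against.** The truncated model is the second-named example in a conditional fallback. The Poisson and negative binomial models that come first keep every village, and so does the zero-inflated model named first in the fallback. The improvement-test clause fits the zero-inflated model, so the truncated option may be loose wording rather than a settled choice. At the planned rate the trigger is almost unreachable. The figure of 1.3 per 1000 is not the article's; it is the product of the state rate and the lowest attempt multiplier. The ratio of 1.00 in case A is built in by placing the whole effect in structural zeros, and nothing in the article supports that mechanism in particular. Even the all-village analysis would miss the effect in most such trials (26.5–43.0% rejection in case A). All of this stands, and it limits the size of the point. It does not make the option valid.

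Three stronger readings are tempting but not supported:

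- A reader might infer that the model can never test population incidence. Cases C and D show that it recovers the ratio when excess-zero shares are equal or counts are Poisson.
- A reader might infer that it removes precisely the villages where the programme worked best. Some zeros are chance, and control villages drop out too (8.4 of 27.4 in the 10%/28% run).
- A reader might infer that the zero-inflated model is equally wrong. It keeps all villages, arm can enter both parts, and an overall rate ratio can be derived. The article does not say that only the count coefficient will be reported, and the rule for choosing between the options may stand in an analysis plan not shown here.

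**Conclusion.** The point holds as an error in a stated fallback. Zero-truncated Poisson regression is not, on its own, an allowance for excess zeros. It conflicts with the intention-to-treat, as-randomised test of population incidence in the same section, and it cannot be judged by the improvement test promised there.

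The bias depends on the excess-zero share differing by arm. It can then hide a true 20% reduction (0.80 estimated as 1.00) or turn no difference into an apparent 20% reduction. The sizes are illustrative, because the zero shares are assumed; the direction follows from the formula in step 2. Where the shares are equal or the counts are Poisson, the ratio is unbiased but villages are lost and, in the plain Poisson case, so is precision.

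The practical risk is low at 10 per 1000. It becomes real mainly if the observed rate is far lower, for example near 1.3 per 1000, or if between-village variation is strong. Severity: should-fix.

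**What to change.** - Delete the zero-truncated Poisson option. Alternatively, allow it only as the positive part of a hurdle model in which the zero part is also modelled by arm.
- State that the primary model keeps all randomised villages, zeros included: Poisson with a gamma village effect, or negative binomial.
- If the zero-inflated negative binomial model is used, report the overall (marginal) incidence rate ratio between arms with its 95% confidence interval. That model need not be removed.

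The cost is a change of wording in the protocol or analysis plan, made before outcomes are examined by arm. No data collection or sample size changes.
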